### Recruitment

Participants are to be recruited from the undergraduate student population of psychology on campus at the Institute of Psychology, Johannes Gutenberg University Mainz, Germany. Flyers are pinned on blackboards and the study is advertised during lectures, seminars and via social networks. Recruitment and enrollment started in October 2015 and will take place continually during the execution of the trial till the expected sample size is achieved (December 2016).

As a means of compensation, the student participants receive course credits. Additionally, all participants who complete more than 80% of the daily questionnaires participate in a raffle of two 100 EUR vouchers for an online shopping website.

### Allocation and blinding

Since we want to reach a sample size of 134 participants, we randomized the total number of participants preliminary to the trial. We used the random allocation rule as a restricted randomization procedure [59] to generate a sequence that randomly orders 67 intervention and 67 control group assignments. Based on this random allocation sequence, consecutively enrolled participants are sequentially assigned to either the control or the intervention condition so that a balanced group allocation should arise at the end of the trial. However, attrition could result in imbalanced group sizes, regardless of the chosen randomization technique. Research assistants who are in personal contact with participants did not prepare the coding list. Preliminary allocation to a condition will not be changed. Due to the wait-list control design, blinding is not possible.

### Statistical analysis

Data analysis will be conducted with Stata 13 (College Station, TX, USA: StataCorp LP) and R (R Development Core Team, Vienna, Austria, 2008) [60]. Analyses include descriptive statistics, mixed models and multilevel VAR models [24]. Missing observations will not be imported for data analysis.

### Primary and secondary outcome analysis

First, the effect of mindfulness training on momentary mindfulness and self-control will be explored. Since Ambulatory Assessment data have a hierarchical structure, where several observations are nested within each day and days are nested within individuals, we use three-level multivariate mixed models including random effects for each level-1 variable (daily observations) allowing for within-day (level 2) and within-person (level 3) variations. In this way, time-varying momentary mindfulness and self-control on level 1 (daily observations) will be predicted by day (level 2) and group (level 3), controlling for age, gender, social desirability and other personality traits at level 3. Significant main effects of the variables day and group would indicate group differences and a change of momentary mindfulness and self-control across time. Furthermore, significant two-way interactions between the continuous variable day (level 2) and the categorical variable group (level 3) would indicate an effect of mindfulness training on momentary mindfulness and self-control relative to the control condition in everyday life.

The secondary outcomes habitual mindfulness and self-control are examined using mixed models. Two-way interactions between laboratory meetings (seven meetings) and group (mindfulness versus control) predicting habitual mindfulness and self-control would indicate differences between groups from one meeting to another. Further additional momentary and habitual measures will be examined in a similar manner.

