### Sample size

The sample size was calculated with a power calculation formula for multilevel models [57] to detect group differences in state and trait mindfulness between individuals. Based on previous research in our laboratory, we assume an unexplained intraclass correlation (ICC) of 0.25 and want to achieve a power of 1 − *β* = .95 and set an alpha level *α* = .05 for a two-sided test to detect a medium difference of Cohens’s *d* = .33 between conditions. The expected medium effect size is based on a meta-analysis (medium effect size Hedge’s *g* = .33) comparing mindfulness-based therapy treatment with other active treatments [58] – since the wait-list control condition participants take part in an Ambulatory Assessment and come to weekly laboratory meetings during its waiting period, we considered the wait-list control condition as an active treatment condition as a conservative estimate for our power calculations rather than an inactive waiting condition. Thus, this leads to a sample size of *N* = 120 to detect medium group differences between individuals. Since prior Ambulatory Assessments in our department showed attrition rates of approximately 10%, the SMASH study aims at a sample size of *N* = 134 to achieve a final total *N* = 120 (control condition *n* = 60; mindfulness intervention *n* = 60).

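### The training effect is tested by day × group, but the random part described for that model names no person-level random slope for day, so the test rejects too often if people differ in their 40-day trends

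*Protocol article*

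**What the plan says.** Under the heading on primary and secondary outcome analysis, the protocol article gives the model for the two momentary outcomes as "three-level multivariate mixed models including random effects for each level-1 variable (daily observations) allowing for within-day (level 2) and within-person (level 3) variations". It then identifies the level-1 variables as momentary mindfulness and momentary self-control, the day as a level-2 predictor and the group as a level-3 predictor. The treatment claim rests on the interaction: "significant two-way interactions between the continuous variable day (level 2) and the categorical variable group (level 3) would indicate an effect of mindfulness training".

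No slope for day that varies between persons is mentioned. For the habitual outcomes, the same section says only that mixed models will be used with a meeting-by-group interaction, and it describes no random part.

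The article speaks of participant-level deviations of coefficients only under self-control networks, for the vector autoregressive models. The sample size section assumes an intraclass correlation ("we assume an unexplained intraclass correlation (ICC) of 0.25") and powers a group difference between individuals. It gives no variance for day or for individual trends.

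**The concern.** The day × group coefficient compares the average 40-day trend of two sets of about 60 people. Its standard error must therefore reflect how much true trends vary from person to person. A person-level random intercept protects a comparison of group means but does not protect a comparison of group slopes. Without a person-level slope, differences between people's trends are absorbed mainly into the day-level variance. They are then averaged out as if each person-day were an independent deviation from the group trend: 120 × 40 = 4,800 person-days instead of 120 people.

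The standard error of the primary treatment contrast is then too small, and the 5% level is not held. It holds exactly only if everyone shares one true trend. Two features of the design make that unlikely. Students enrol continuously over more than a year, so their 40-day windows fall in different parts of it. Home practice in the intervention arm is optional and may vary in frequency.

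**Working it through.** **The plan's own figure.** With d = 0.33, two-sided alpha 0.05 and power 0.95, the total N for independent observations is 4 × ((1.96 + 1.645)/0.33)² ≈ 477.3. Multiplying by ICC + (1 − ICC)/m with ICC = 0.25 gives 120.8 for m = 240 prompts and 119.3 as m grows without limit. Both agree with the stated 120. With 60 per arm and m = 240, power is 0.949. Allowing for 10% attrition, 120/0.9 = 133.3, so 134. The stated figures reproduce, but for a difference in person means and not for a difference in slopes.

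**Inputs to the type I error check.**
- From the article: 60 per arm, 40 days, 6 prompts a day, and a person share of variance of 0.25 (reading the stated ICC that way).
- Assumed, because the article does not give them: total variance 1; day share 0.05, 0.10 or 0.20, with the rest of the remaining 0.75 at prompt level; linear trends; independent day effects; complete data; one outcome at a time. The between-person SD of true change from day 1 to day 40, called s, runs from 0 to 0.5 total SD.

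**Formula.**
- The sum of squares of days 1 to 40 about their mean is 5330, and the slope variance is (s/39)².
- The variance of a person-day mean is v = day variance + prompt variance/6.
- Put x = (s/39)² × 5330 / v.
- The true variance of the interaction is proportional to 1 + x. The model without the slope estimates it as proportional to 1 + x/39, because the omitted slope variation is spread over 39 within-person degrees of freedom.
- The understatement is V = (1 + x)/(1 + x/39).
- Actual type I error = 2 × (1 − Φ(1.96/√V)).

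**One case in full.** For day variance 0.10, v = 0.10 + 0.65/6 = 0.2083. At s = 0.2, x = (0.04/1521) × 5330/0.2083 = 0.673 and V = 1.673/1.017 = 1.64. Then 1.96/√1.64 = 1.53, and type I error is 12.6%.

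**Results without the person-level slope (V, then type I error).**

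| SD of change s | day share 0.05 | day share 0.10 | day share 0.20 |
|---|---|---|---|
| 0 | 1.00, 5.0% | 1.00, 5.0% | 1.00, 5.0% |
| 0.1 | 1.20, 7.4% | 1.16, 6.9% | 1.12, 6.4% |
| 0.2 | 1.80, 14.4% | 1.64, 12.6% | 1.46, 10.5% |
| 0.3 | 2.76, 23.8% | 2.42, 20.8% | 2.03, 16.8% |
| 0.4 | 4.02, 32.8% | 3.45, 29.2% | 2.79, 24.0% |
| 0.5 | 5.51, 40.4% | 4.70, 36.6% | 3.72, 30.9% |

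**Checks.** Simulation with 4,000 null trials per setting agreed. At day share 0.10 it gave 7.5%, 12.8%, 20.4%, 28.3% and 36.7% for s = 0.1 to 0.5. Testing group on person-specific slopes gave 4.1% to 5.6% in every setting.

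A rough check fitted REML mixed models to day means with about 80% of prompts answered. Without the slope it gave 19% at s = 0.3 (81 trials) and 30% at s = 0.5 (76 trials), against 7% with the slope in both cases. With so few trials, these figures show only the direction and order of size.

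**The case against.** The strongest reply is that the article does not exclude a random slope. Its wording says the models include certain random effects, and it does not say that there are no others. It never uses the word intercept, and in the network section random effects do cover person-specific coefficients. It is also a condensed journal article, and a complete random-effects specification is normally left to an analysis plan, which is not at hand. Part of this stands: the absence of a day slope is a reading of the sentence and not something it states. But the article is not silent here. It chose to describe the random part, tied it to the level-1 outcomes, and left out the one term on which its own effect test depends. An analyst following the text could reasonably fit intercepts only.

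Second, the size depends on figures outside the document. This stands in full. Neither the SD of change nor the day variance is given, and at an SD of 0.1 the inflation is slight.

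A reader might also infer that the thousands of prompts are treated as independent. They are not, because the day level already clusters prompts. The unit wrongly taken as independent is the person-day.

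**Conclusion.** The point holds as a defect in the described model, conditional on its plain reading. If the primary model is fitted with random effects for the outcomes at day and person level and no person-level slope for day, the day × group test is anti-conservative whenever true trends differ between people. Under the assumptions listed, type I error is about 6–7% at a change SD of 0.1, 10–14% at 0.2, 17–24% at 0.3, 24–33% at 0.4 and 31–40% at 0.5. With the slope it is about 5%. The true size is unknown.

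Three stronger conclusions are not supported:
- That type I error will be several times 5%. This needs a change SD of roughly 0.25 to 0.3 or more, which nothing in the article establishes. Even the largest value examined, about 40%, does not make a false claim more likely than not.
- That the sample size is wrong on this account. It reproduces for the between-person contrast it was computed for.
- That the habitual-outcome models share the fault. No random structure is stated for them, so there the point is only a request for clarification.

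**What to change.** State in the primary analysis that each momentary outcome has random intercepts at person and day level plus a person-level random slope for day, correlated with the person intercept. Add the fallback: if the model does not converge, estimate a slope for each person and compare these between groups. If a random slope was intended all along, the same sentence settles the matter. For habitual mindfulness and self-control, say which random effects the mixed models contain, including whether the effect of meeting varies between people.

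The cost is one sentence, some convergence work and wider intervals. The widening is about √V: some 6 to 10% if the SD of change is 0.1 (√1.12 = 1.06, √1.20 = 1.10), and more if trends differ more. In that case the wider interval is the correct one.

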### Intervention

The mindfulness training starts 1 week after the first laboratory meeting. From this time on, participants from the intervention and control conditions take part in different laboratory meetings (separated from each other) to minimize the chance of contamination between conditions. Mindfulness is practiced with a computer-based guided-breathing meditation for five weekly sessions in which one’s own breath has to be counted repetitively from one to nine [26]. A “click” sound occurs if a breath was miscounted guiding attention back to the current moment and the Breath-counting Task [26]. After the first mindfulness training session, participants in the intervention condition are also able to practice mindfulness (breathing meditation or body scan) at home by listening to an audio file via their smartphones. Each episode of ambulatory mindfulness practice is saved in a data file in order to assess how often mindfulness is practiced during the treatment period. After the third training session, participants perform an informal mindfulness task, which is used in mindfulness-based stress-reduction programs [15] to apply mindfulness in everyday life.

Since only healthy participants are enrolled in the SMASH study, we do not expect any harm from the low-level mindfulness intervention. For this reason, there are no criteria for discontinuing or modifying the intervention.

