#### Habitual mindfulness

As a further secondary outcome, habitual mindfulness is assessed with the original version of the MAAS [27], which consists of 15 items. A validated German version of the MAAS is used in this study (Cronbach’s *α* = .83; test-retest reliability *r* = .82) [28]. The self-report of habitual mindfulness is collected at the seven weekly laboratory meetings.

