#### Laboratory sessions

During the first laboratory session, all participants complete self-report questionnaires and a Breath-counting Task [26] which is conducted on computer. One week after the first laboratory meeting, both intervention and control condition participants come to five weekly laboratory meetings completing questionnaires regarding self-reported dispositional mindfulness and self-control. A maximum of three participants can take part in a laboratory meeting at once. From the second laboratory meeting on, only the intervention condition starts practicing mindfulness with a computer-based guided-breathing meditation for 12 min at five weekly appointments. At the seventh and final laboratory meeting, a post-intervention measurement takes place. During the final measurement, questionnaires that were completed within the first laboratory meeting are answered again. Also the Breath-counting Task [26] is conducted by both control and intervention conditions comparing counting accuracy between them as well as before and after mindfulness training. The seven laboratory meetings are conducted on computers with the operating system OS X El Capitan, Version 10.11 and a screen resolution of 1920 × 1080. The software Inquisit 4 (Millisecond Software, 2014) is used to present the questionnaires on the screen.

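### The habitual mindfulness and self-control models leave the pre-training meeting unadjusted; a common mean at meeting 1, or its value as covariate, would give a modest gain in precision at no data cost

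*Protocol article*

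**What the plan says.** Under Primary and secondary outcome analysis, the habitual outcomes are to be examined by mixed models, and the evidence for an effect is "Two-way interactions between laboratory meetings (seven meetings) and group (mindfulness versus control) predicting habitual mindfulness and self-control". Covariates (age, gender, social desirability, personality) are listed for the momentary outcomes only. For the habitual outcomes the section names neither a baseline covariate nor a constraint on the arm means at the first meeting. Further measures are to be handled likewise.

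Both habitual scales are completed at all seven weekly meetings. On timing, the Intervention section says "The mindfulness training starts 1 week after the first laboratory meeting", and Laboratory sessions says "From the second laboratory meeting on, only the intervention condition starts practicing mindfulness with a computer-based guided-breathing meditation". Meeting 1 is therefore before training, and practice begins at meeting 2. The first-meeting questionnaires are repeated at meeting 7.

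The retest correlation given for the German MAAS is "test-retest reliability *r* = .82"; the value given for the SCS-K-D is the same.

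**The concern.** In a randomised comparison the arms have the same expected mean before treatment. A meeting-by-group model over all seven meetings, in its usual form, does not use this: it estimates a separate arm difference at meeting 1 and subtracts it in full. The final-meeting effect is then the difference between arms in raw change from meeting 1. Full subtraction is the best use of a baseline only when it correlates perfectly with the follow-up. At any lower correlation, subtracting the right fraction gives a smaller standard error from the same data.

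At stake is precision on the secondary outcomes and on the questionnaires repeated at the end. Validity is not at stake. The point has some weight because the Sample size section names trait as well as state mindfulness as what the trial is powered for.

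**Working it through.** **1. The plan's own figure.** Inputs from Sample size: "set an alpha level *α* = .05 for a two-sided test", "want to achieve a power of 1 − *β* = .95", a difference of .33, and "we assume an unexplained intraclass correlation (ICC) of 0.25". For independent observations, n per arm = 2(1.960 + 1.645)²/.33² = 238.7. Multiply by ICC + (1 − ICC)/m for the mean of m readings per person:

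- m = 240 (six prompts on 40 days): .2531 × 238.7 = 60.4, so 61 per arm.
- Very large m: .25 × 238.7 = 59.7, so 60 per arm, N = 120.

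Allowing for 10% attrition, 120/.90 = 133.3, so 134. The stated N reproduces. It rests on a person mean over many readings, so the figures below concern a different contrast and do not correct it.

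**2. Final-meeting contrast on a habitual scale.** Assumptions: SD 1, 60 per arm, complete data, r = .82 between all meetings, meeting as a factor, a true difference of .33 SD. The variance of an arm difference is the per-person variance × 2/60.

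| Analysis of meeting 7 | Per-person variance | SE | Power |
|---|---|---|---|
| No use of baseline | 1 | .1826 | 44% |
| Planned: change from meeting 1 | 2(1 − r) = .36 | .1095 | 85% |
| Common mean at meeting 1, or meeting 1 as covariate | 1 − r² = .3276 | .1045 | 88% |

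Power is Φ(.33/SE − 1.96). The ratio of the last two variances is (1 + r)/2 = .91: variance 9% lower and SE just under 5% lower.

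**3. Sensitivity to the correlation.** The article does not give the retest interval behind .82, so a range is needed. With equal correlation between meetings, the reduction in variance is 1 − (1 + r)/2:

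- r = .9: 5%
- r = .7: 15%
- r = .5: 25%
- r = .25: 37.5%

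If instead .82 holds between adjacent meetings and decays by powers, the correlation between meetings 1 and 7 is .82⁶ = .304. The reduction is then 35% (SE .2154 to .1739).

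**4. Other readings of the interaction.** At r = .82:

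- Joint test of all meeting-by-group terms, with an effect that rises linearly after meeting 2 to .33 at meeting 7: power .883 with a free arm difference at meeting 1, .898 with a common mean there.
- Meeting as a linear term: the variance of the slope difference is 1.068 times as large without the common start, so the constraint saves about 6%.

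**5. Measures taken only at the first and last meeting.** With two occasions, the interaction is exactly the difference in change scores. Adjusting for meeting 1 again leaves (1 + r)/2 of that variance. For KIMS, with retest values of .78 to .86 in the article and assuming it is taken at these two meetings, the factor is .89 to .93, a reduction of about 7 to 11%.

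**The case against.** The strongest reply is that meeting by group over all visits is a standard, unbiased analysis of secondary outcomes, and that a condensed article may leave the parametrisation to an analysis plan. The section does not say whether meeting is a factor or linear, and it writes out a group main effect only for the momentary outcomes. The free arm difference at meeting 1 is therefore the usual reading of the text rather than a stated term. All of this stands, and it limits the size and weight of the point. It does not remove it: the article states a model for these outcomes, and a more precise one is available from the same data.

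A reader might infer that meetings 1 and 2 are both baselines. On the assumptions of step 2, a common mean at both gives per-person variance 1 − r²/((1 + r)/2) = .2611, SE .0933 and power 94%. The SE is 15% lower than planned, equivalent to about 38% more participants. The documents do not support this reading:

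- They do not say that the meeting-2 questionnaires come before that day's first practice.
- Meeting 2 follows an unblinded allocation, with the arms already attending separately, and the outcomes are self-reports. A common mean there assumes no expectation effect. With an illustrative arm difference of .10 SD at meeting 2, which carries weight r/(1 + r) = .45, the estimate would shift from .33 to .285 and power would fall to 86%.
- Most of the gain is averaging. A free model contrasted with the mean of meetings 1 and 2 has per-person variance .27, SE .0949 and power 93.6%. The constraint itself is worth only 3.4% in variance.

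A reader might also infer that the plan wastes its baseline. It does not: change from meeting 1 already takes the SE from .1826 to .1095.

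**Conclusion.** The point holds as a modest efficiency gain on secondary outcomes. The stated analysis is valid. Bringing in meeting 1 as a common starting point or a covariate lowers the variance of the final-meeting contrast by about 9% and raises power from 85% to 88%, given r = .82 between all meetings, 60 per arm, a difference of .33 SD carried over to the habitual scales, equal SDs, complete data and meeting as a factor. The gain grows if the correlation between meetings is lower and shrinks to between one and two points of power for the joint test. It also requires that the meeting-1 questionnaires precede knowledge of allocation. The Procedure section places allocation in that same session, after consent, and does not settle the order; the arms attend separately only from the start of training.

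**What to change.** In the mixed models for MAAS and SCS-K-D, give both arms a common mean at meeting 1 (no group effect there) and estimate arm differences from the later meetings. Alternatively, use the meeting-1 value as a covariate with the later meetings as outcomes. For questionnaires taken only at meetings 1 and 7, analyse meeting 7 adjusted for the meeting-1 value. State whether the meeting-1 questionnaires were completed before participants learned their allocation.

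Use meeting 2 as a second baseline only if its questionnaires preceded the first practice and the sponsor accepts that no expectation effect arises after unblinded allocation; otherwise keep it as a follow-up occasion.

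The cost is a change of model wording before the data are analysed. No further data or participants are needed. If a separate analysis plan already specifies this adjustment, a sentence saying so is enough.
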